### Harms

Adverse events refer to adverse medical events that occur in patients of this clinical trial after receiving the medications. In this study, an adverse event will be considered to the therapy from the time when patients sign the informed consent form to 1 month after the end of treatment. Assessing the nature and determining the severity of adverse events will be conducted in accordance with “expert consensus on diagnostic criteria for postoperative complications of gastrointestinal cancer in China”. To assess adverse events and their causal relationship to therapy, the investigator will evaluate the possible associations between adverse events and trial medications. The following five criteria will be used to determine the results: the time of occurrence of adverse events coincides with the time of administration, adverse events are related to known adverse reactions of the medication, adverse events cannot be explained by other reasons, adverse events disappear after discontinuing therapy and adverse events are reproduced after medication re-administration. The results documented as positive, relevant and possibly related will be deemed adverse reactions. The incidence of adverse reactions will be calculated accordingly. To record, process and report adverse events, the investigator will document any adverse events. Records of adverse events will include a description of adverse events and all related symptoms, time of occurrence, severity, duration, measures taken, the results and final outcomes. The reporting methods and treatment measures for severe adverse events will be classified as severe adverse events if they meet one or more of the following criteria: death, life-threatening (e.g., immediate risk of death), prolonged hospitalization or hospitalization, permanent or severe disability, congenital malformations or defects, some events that have not yet caused death, danger to life or hospitalization; we will also consider severe adverse events perpetrated by a physician if they cause harm to the patient or require medication or surgical treatment to avoid the above situation. For any severe adverse events during the clinical trial, the investigator will file a report of severe adverse events within 24 h and report in writing to the Ethics Committee, the superior authorities. The written report will include the time, severity, duration, measures taken and outcomes of serious adverse events.

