Patients who violate the principles of treatment after enrolment (e.g., violate the criteria for enrolment and discharge or do not comply with the medication or surgical arrangement for the study duration);Patients who were unable to undergo surgery for various reasons after enrolment (reasons will be recorded);Patients experiencing nonstudy-related complications such as drug allergies after enrolment;Patients who the investigator does not consider appropriate for continuation (reasons for withdrawal need will be documented);Patients who develop severe complications or unacceptable adverse reactions; andPatients who were unable to undergo elective surgery due to sudden aggravation or other reasons after enrolment.

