### Treatment protocols

All eligible patients with colorectal cancer will be randomly assigned to the test group or the control group in a 1:1 allocation ratio. Participants in both groups will undergo similar perioperative procedures with the exception that the test group will receive oral antibiotics before surgery. For the test group, antibiotics will be given (both neomycin 1 g and metronidazole 0.9 g) the day before surgery (at 1 pm, 3 pm and 10 pm). The control group will take the same dose of placebo as the experimental group (Table 1). Intraoperative anal water injection experiments and infiltration by ICG fluorescence were performed to ensure the quality of the anastomosis.

**Table 1 Tab1:** The medication and usage in this experiment

		Time of drug administration		
Drug name	Dose	13:00	15:00	22:00
Neomycin/placebo	1 g			
Metronidazole/placebo	0.9 g			

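### The adverse reaction rate rests partly on dechallenge and re-administration criteria that tell little about a one-day, three-dose course; all adverse events by randomised arm would be the better main safety comparison

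*Protocol article*

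**What the plan says.** The Harms section of the protocol article sets out how the investigator decides whether an adverse event was caused by trial medication: "The following five criteria will be used to determine the results". The five are:

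1. Timing: "the time of occurrence of adverse events coincides with the time of administration".
2. and 3. Known profile and no alternative cause: "adverse events are related to known adverse reactions of the medication, adverse events cannot be explained by other reasons".
4. and 5. Dechallenge and rechallenge: "adverse events disappear after discontinuing therapy and adverse events are reproduced after medication re-administration".

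Events in three causality grades, the lowest being possibly related, are then deemed adverse reactions, and "The incidence of adverse reactions will be calculated accordingly". This is the only adverse event rate that the section names. The section also says that any adverse event is documented, whatever its cause.

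Treatment protocols gives the exposure in the active arm: "antibiotics will be given (both neomycin 1 g and metronidazole 0.9 g) the day before surgery (at 1 pm, 3 pm and 10 pm". Controls take placebo on the same schedule.

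The termination criteria at the end of Inclusion and exclusion criteria list "Patients experiencing nonstudy-related complications such as drug allergies after enrolment".

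**The concern.** Dechallenge and rechallenge suit a drug taken over time, which can be stopped when an event appears and restarted when it has gone. Here the whole course runs from 13:00 to 22:00 on one day and surgery follows the next day. Nobody decides to stop the drug because of an event after surgery, since it has already ended for everyone, and no restart is planned. Two of the five criteria therefore give little information about whether drug or surgery caused an event, yet they feed the one adverse event rate that Harms fixes.

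A rate built on such attribution is hard to interpret. The trial has a direct way to separate drug from surgery, because both arms have the same operations and differ only in antibiotic or placebo. A comparison by randomised arm needs no judgement on cause.

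A second, smaller matter is the termination list. It can be read as labelling drug allergies unrelated to the study in advance, although the study drugs are antibiotics and Harms treats a known reaction to the medication as evidence of relatedness.

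**Working it through.** The article states no expected adverse reaction rate, so there is no figure to reproduce. The check sets the criteria against the dosing schedule.

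**Inputs.** Five criteria, and a threshold that counts events down to possibly related (Harms). Three dosing times on one day before surgery, with matching placebo (Treatment protocols, Table 1). Patients, doctors, data collectors and analysts blinded (Blinding).

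**Criterion by criterion.**

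| Criterion | Can it discriminate with this regimen? |
|---|---|
| Timing | Yes; the exposure window is short and exact |
| Known reaction profile | Yes |
| No other explanation | Yes for events on the dosing day; harder after surgery, which explains many events |
| Disappears after stopping | Poorly; met by any event that resolves, whatever its cause |
| Recurs on re-administration | Poorly; no dosing after withdrawal is planned |

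**Effect on the rate.** The article does not say how many criteria must be met, or which combination gives which grade. Three assumed readings show the range:

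- All five required: almost no event could qualify, and the rate would be close to zero.
- One or more of the first three enough for possibly related: nothing is lost by the absence of the last two.
- Dechallenge alone enough: every event that resolves would count, and the rate would be inflated by surgical events.

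The inclusion of possibly related events points away from the first reading.

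The same can be put in symbols. Let b be the background event proportion in both arms, d the additional proportion caused by the drug, p0 the chance that a background event is graded as related, and p1 that chance for a drug-caused event. Blinding makes p0 and p1 the same in both arms. The reported test-arm rate is then p0·b + p1·d. It exceeds the true drug-caused proportion d when p0·b > (1 − p1)·d and falls short when the inequality is reversed. The reported difference between arms is (p0·b + p1·d) − p0·b = p1·d, which equals d if every drug-caused event is graded at least possibly related. The comparison of all events estimates d without needing p0 or p1. The documents give none of these quantities.

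**What is already compared without a causality filter.** Efficacy assessment indicators makes 30-day complications by Clavien–Dindo, including other organ complications, and readmission within 30 days secondary outcomes. Statistical analysis gives secondary variables an effect estimate with a 99% confidence interval. Events that look like postoperative complications are therefore compared by arm however the investigator attributes them. What remains uncovered is adverse events outside those outcomes.

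**The case against.** The strongest case on the other side has five parts.

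- The rule from criteria to grades is a detail that a full protocol or case report form commonly carries and an article leaves out. This stands: its absence is not itself a fault. It does mean that the direction of any distortion cannot be read from the article.
- An all-event table by arm is commonly left to the statistical analysis plan. This also stands, and the point is not that such a table is missing. It is that the rate the article does fix is the weaker of two available measures.
- Re-administration is not wholly absent. An acute reaction after the 13:00 dose could recur after a later one, and Table 2 marks oral antibiotics as if necessary at unplanned follow-up. This stands in part: recurrence between same-day doses is possible, but it is not re-administration after withdrawal.
- Safety does not rest on this rate alone. All events are documented, severe events are reported within 24 h on criteria that do not depend on causality, attribution is blinded, and the monitoring committee has unmasked access to the data. This stands, and limits the consequence.
- The termination wording on allergies may mean allergies to drugs other than study medication, and the same list separately names unacceptable adverse reactions. This is a fair reading. The wording is ambiguous; it does not show that study-drug allergies are excluded from assessment.

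A reader might go further and infer that the adverse reaction rate will understate harm, or that antibiotic effects resembling surgical complications will drop out of the comparison. The documents support neither. The five criteria are not stated to be jointly required, possibly related events count, an automatically met dechallenge criterion can push attribution up, and postoperative complications are compared by arm regardless of cause.

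**Conclusion.** The concern holds as a minor point. Two of the five causality criteria discriminate poorly for a three-dose, one-day preoperative course, so the planned incidence of adverse reactions can be distorted upwards or downwards. Neither the direction nor the size can be determined from the article, since both depend on a rule from criteria to grades that it does not give. The gap is confined to adverse events outside the 30-day complications and readmissions. The conclusion assumes that dosing follows Treatment protocols, with no planned study medication after the 22:00 dose. The allergy wording is an ambiguity to be reconciled, not a demonstrated exclusion.

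**What to change.** In Harms, state that the main safety comparison is the proportion of patients with any adverse event, and with any severe adverse event, by randomised arm regardless of causality, with risk difference and 99% confidence interval. A breakdown by type of event would keep any reduction in infective complications from masking an excess of other events in the total. Keep investigator-judged adverse reactions as a secondary summary based on timing, known profile and alternative cause, without the dechallenge and re-administration criteria.

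Reconcile the allergy item in the termination criteria with Harms, so that it is clear that a suspected allergy to study medication is assessed for relatedness. This concerns classification only; whether such a patient continues is not addressed here.

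The cost is protocol wording and one extra table, since Harms already has all events documented. One check is needed: Table 2 has no mark for recording adverse events on the preoperative day, when the drug is taken, whereas Harms counts events from consent. Those two places should agree for the comparison to include the dosing day. The downside is that reported event rates will be higher in both arms, because surgical events are included.

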### Data collection and observation indicators

Baseline data (collected medical history and demographics, including patient sex, age and contact number; detailed medical history, treatment history, body mass index (BMI); routine blood tests; inflammation index; coagulation test (prothrombin time (PT), activated partial thromboplastin time (APTT), thrombin time (TT), fasting blood glucose (FBG), D-dimer, international normalized ratio (INR)) will be recorded. A premedication imaging assessment test (CT/MRI) including enhanced CT or MRI of the chest, abdomen and pelvis will be completed within 2 days before medication administration. All suspected lesions will be evaluated by imaging tests.

### Follow-up

The follow-up phase will start from the first day after surgery. Patients who do not recover from adverse reactions will be treated and followed up closely until they return to the first level or complete recovery specified in the "expert consensus on diagnostic criteria for postoperative complications of gastrointestinal cancer in China". Follow-up tests include the following: incision condition, RBC count, WBC count, haemoglobin, lymphocytes, neutrophils, eosinophils, CRP, calcitonin, TNF-α, IL-6, and imaging (enhanced CT or MRI of the chest, abdomen and pelvis). In addition, quality of life will also be assessed.

### Patient protection/written informed consent forms

Both parties ensure the protection of the patient’s personal records. Except for documents required by law, patient names are not included in any form in tabular reports, publications or any type of research publication document. Informed consent will be formulated in strict accordance with Chinese laws and regulations. Written informed consent, including all changes made throughout the study, must be preapproved by the Internal Review Board/Independent Ethics Committee before inclusion in the study. Medical staff at each centre will obtain a signature with written informed consent from each patient (if the patient is unable to make their own decision for various reasons, the immediate family will decide on their behalf) prior to any specific activities related to the study. Researchers at each centre will submit and keep original copies of all written informed consent forms signed by patients and provide additional copies to patients or their immediate family members for their records.

### Monitoring of the study

Before the start of the study, the personnel of the project unit will visit the research centre and discuss with the researcher (and/or other research-related personnel) their responsibility for the research programme and the responsibility of the project undertaking unit or representative.

During the study period, the project undertaker or the supervisor representing the project will regularly contact the research centre for a number of reasons including the following: providing information and technical support; establishing randomized grouping as required; confirming that the investigator complies with the study plan, that data on the CRFs are accurately recorded, and that dosage of drugs being used is checked; and carrying out original data analysis (e.g., the data on CRFs are related to the records of patients in the hospital, and the research will compare these with other records). This requires direct access to the original records of each patient (e.g., clinical charts).

The investigators will not have access to data until the study is completed and data are analysed. A data monitoring committee will be established at Xijing Hospital, who will assess the results and safety of the treatments performed at all centres.

Representatives authorized by project undertakers, regulatory departments, and independent ethics committees may visit the centre for inspections, including verifying the original data every half year. The purpose of the inspections of the site and personnel is to systematically and independently examine all research-related behaviours and documents, to determine that these behaviours have been managed and that the data have been analysed, recorded and accurately reported in accordance with the research programme, GCP, ICH guidelines and other regulatory requirements.

### Interim analysis plan

A planned interim analysis of the primary endpoint will be performed when 750 patients are enrolled in the study and the postoperative 30-day evaluation is completed. Interim analyses were performed by an independent statistical team. The statistical team will report the analytical results to DSMC (data and security monitoring committee). The DSMC will have unmasked access to all data and will discuss the results of the interim analysis with the principal investigator at all participating centres at an investigator joint meeting. The decision to continue the study was made at a joint investigator meeting.

Interim analysis will be conducted when study enrollment is 50% complete, or 12 months after formal initiation. This study should be terminated if one of any of the following occurs: enrollment ≤ 30%.

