### Randomization/Assignment of interventions

Randomization was stratified by centre. Once informed consent is obtained, randomization will be performed via a centrally managed database. After receiving the patient grouping information, designated researchers at each centre will prepare trial drugs or placebo for patients according to the assigned group. In this process, only the researchers are informed about the grouping of patients. They will sign a confidentiality agreement and will not participate in any other links of the trial to ensure that they will not have any impact on the study. After collecting all the data, the designated researcher named the two groups A and B. The analyst will analyse the primary and secondary results without knowing the group name. Only after the analysis of the primary and secondary results can complete blindness be eliminated and ineffective blinding events recorded (for example, the study nurse discloses the patient’s specific medication to the doctor).

The nurses provided the patients with oral antibiotics for the experimental group and placebo for the control group in the ward.

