### Blinding (masking)

The blind level was set as double-blind. All patients, doctors, data collectors and analysts will be unaware of the grouping of patients.

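### The interim plan takes the interim primary-endpoint results to the principal investigators of all centres and has continuation decided at their meeting, against the rule that investigators see no data before the study is analysed

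*Protocol article*

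**What the plan says.** The Interim analysis plan gives two statements of timing: "A planned interim analysis of the primary endpoint will be performed when 750 patients are enrolled in the study" and have completed their 30-day evaluation, and "Interim analysis will be conducted when study enrollment is 50% complete, or 12 months after formal initiation". On who does the work, it says "Interim analyses were performed by an independent statistical team", which reports to the DSMC. The DSMC sees all data unmasked and then "will discuss the results of the interim analysis with the principal investigator at all participating centres at an investigator joint meeting". The section adds: "The decision to continue the study was made at a joint investigator meeting".

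Monitoring of the study, the section just before it, says: "The investigators will not have access to data until the study is completed and data are analysed".

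Two other sections bear on the consequences. Efficacy assessment indicators makes radiography for leakage follow from clinical suspicion. Preoperative management leaves the choice of procedure, extent of dissection and type of reconstruction to the operating surgeon.

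**The concern.** An independent statistical team and an unmasked committee exist so that the comparison can be watched without those who run the trial learning it. Here the route is set up correctly as far as the committee and is then opened to the principal investigator of each centre.

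Four things are at stake once the interim trend is known:

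- **Recruitment.** Centres may change whom they approach, or how keenly.
- **Conduct.** Perioperative choices left to local judgement may drift.
- **Ascertainment.** The primary endpoint depends on someone suspecting a leak and ordering imaging, and that threshold can shift.
- **Continuation.** The decision is made at a meeting of the people conducting the trial, after they have heard the results.

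A site that reads the monitoring section would expect to see nothing. A site that reads the interim section would expect an invitation to discuss the results.

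**Working it through.** The main check is a comparison of the text. The arithmetic only sizes the part of the trial that is exposed.

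**1. The two rules side by side**

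| Question | Monitoring of the study | Interim analysis plan |
|---|---|---|
| Do investigators learn results before the end? | No, not until completion and analysis | Yes, at a joint meeting during the trial |
| Which investigators? | Investigators in general | The principal investigator at every centre |
| Where is continuation decided? | Not stated | At the joint investigator meeting |

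One could try to read the word data in the monitoring rule as the raw dataset only, so that hearing a result is not access. That is a weak reading, because the rule would then forbid the records while allowing the one summary it most needs to protect.

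**2. What would be disclosed**

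The interim analysis is of the primary endpoint, in a two-arm superiority trial, presented by a committee with unmasked access. A comparative result is the natural content. No section confines the DSMC to pooled figures or to a recommendation. Labelling the arms A and B would still show the size of the difference.

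**3. Share of the trial exposed**

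Inputs: 1500 patients in total (Study design) and a look at 750 (Interim analysis plan).

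The plan's own figure reproduces: 750/1500 = 0.50, which agrees with the 50% in its second timing statement.

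If E patients have been enrolled when the meeting is held, the exposed share is (1500 − E)/1500.

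- *750-patient trigger:* E is at least 750, so the share is at most (1500 − 750)/1500 = 50%. It is lower if enrolment goes on while the 30-day evaluations are completed. No pause in recruitment is stated.
- *12-month trigger:* E depends on the speed of recruitment, which the article does not give. The share is unknown and exceeds 50% if fewer than 750 have been enrolled by then.

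**4. How few events the meeting would hear about**

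With 1:1 allocation, 375 patients per arm have been evaluated at the 750-patient look. The article gives a leakage rate of 2.3% and a margin of 1 percentage point. The pairs below are assumptions built from those two figures.

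- 3.3% v 2.3%: 375 × 0.033 = 12.4 and 375 × 0.023 = 8.6, about 12 v 9 leaks.
- 2.3% v 1.3%: 375 × 0.023 = 8.6 and 375 × 0.013 = 4.9, about 9 v 5 leaks.

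The trend disclosed would rest on roughly 14 to 21 events in all. This describes what would be disclosed. It is not an estimate of bias.

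**The case against.** The strongest defence is that an aggregate result does not unmask anyone. Both arms take masked drug or placebo, and only the DSMC is given unmasked access. A surgeon who knows the overall difference, but not a patient's arm, may order more or fewer scans for everyone. That changes sensitivity and event counts in both arms alike. This stands, and it rules out three stronger readings.

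- *That leaks would be shifted in one arm, so that a bias in the risk difference can be computed.* This needs individual allocation to be known or guessed, and the interim section does not provide for that. No percentage-point bias is claimed here.
- *That the interim plan also contradicts the blinding sections.* Blinding (masking) says "All patients, doctors, data collectors and analysts will be unaware of the grouping of patients", which concerns patients' grouping. The sentence in Randomization/Assignment of interventions, "Only after the analysis of the primary and secondary results can complete blindness be eliminated", concerns full unblinding around the final analysis. An aggregate interim result breaches neither directly. The direct conflict is with Monitoring of the study alone.
- *That the trial could no longer be reported as double-blind.* Patient-level masking could stay intact. What suffers is the confidentiality of the interim results.

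Other limits are also fair. The article does not say in terms that figures by arm are shown, nor that anyone votes. It names principal investigators, not all staff of a centre. The risk of stopping on a chance result depends on stopping boundaries as well as on who attends, and the change proposed here does not address boundaries.

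It could also be said that an article condenses the full protocol. That excuses missing detail. It does not excuse a procedure that is stated outright and contradicted in the neighbouring section.

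**Conclusion.** The concern holds as a contradiction between Monitoring of the study and the Interim analysis plan, and as a stated procedure that weakens the trial's integrity. Interim primary-endpoint results would reach the principal investigators of all centres, and continuation would be decided at their meeting. The exposed part is up to about half of the 1500 patients under the 750-patient trigger and is unknown under the 12-month trigger.

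The conclusion assumes that the results discussed are the between-arm comparison, which is the natural reading but is not spelled out. The effects on recruitment, conduct, leak work-up and continuation are risks and have not been measured. Disclosure cannot be undone, so the text needs correcting before the interim meeting is held.

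**What to change.** Rewrite the Interim analysis plan along these lines:

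1. The independent statistical team sends comparative results to the DSMC only, which considers them in closed session.
2. The DSMC issues only a recommendation (continue, modify or stop), without comparative figures, to a named body that has not seen the comparative results. That body decides.
3. Investigators receive only the decision.
4. Delete the discussion of results and the continuation decision at the joint investigator meeting.

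The rule in Monitoring of the study can then stand unchanged.

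The cost is mainly amended wording in the protocol and in any DSMC charter. The statistical team and the DSMC are already planned, and no patients or visits are added. The article describes no steering committee, so the deciding body has to be designated. The small downside is that investigators lose their say on continuation.
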